#### Sample size

Power calculations to determine sample size were carried out using G Power 3.1.9.4 software (version 3) statistical power calculator. This indicated that a minimum sample size of 871 was needed to detect a weight loss difference of 1.9 kg between baseline and follow-up with a power of 90%, at α = 0.05 and effect size of 0.11. These estimations were derived from a previous study investigating the effect of cognitive behaviour therapy lifestyle intervention on weight and other health outcomes [33]. An additional sample of 15% was added to account for unpredictable effect on statistical power of clustering cases by site. To allow for attrition and ensure sufficient power during the follow up period, an attrition rate of 30% was estimated between enrolment and follow up assessment, bringing the total sample size to 1303 participants.

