### Data analysis

Statistical analysis of quantitative data will be conducted using Statistical Package for Social Sciences (SPSS) IBM statistics (version 26, SPSS UK Ltd. Chertsey, UK). The normality of continuous variables will be checked using QQ-plots and the Shapiro-Wilk test. All tests will be carried out at the 95% confidence interval and in all analyses, a threshold of *p* < 0.05 will be considered statistically significant. Chi-square tests for independence will be used for comparing categorical variables such as sex and employment status. Means and standard deviations will be computed for continuous variables including age, body weight and BMI. Paired t-tests and repeated measures analysis will be used to examine the effect of the intervention on body weight and BMI of participants over time. Correlations and regressions or non-parametric equivalents as appropriate will be used to examine the relationships between continuous variables. The contribution of demographic variables to predicting BMI and behaviour change will be assessed using multiple linear regressions. The analysis will be conducted using intention-to-treat principles and for completers only.

Qualitative data (photos and transcript form semi-quantitative interview) will be analysed using NVivo Pro 12.5 (QSR International, 2020), which permits the coding of photos as well as text. Interviews will be audio recorded with the participants’ consent and transcribed. Thematic analysis and content analyses using both deductive and inductive approaches [48] will be used to test initial theories while allowing for emergence of new themes, and will include stages of familiarisation, coding, indexing and charting, mapping and interpretation. The deductive analysis will enable to test whether data are consistent with prior assumptions and theories identified during the development of the initial programme theory. The inductive approach which is guided by specific evaluation objectives will allow research findings to emerge from the frequent, dominant, or significant themes inherent in the raw data.

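### Intention-to-treat is promised for weight and BMI, but the paired t-test needs both weights, and the article does not say how the expected 30% without a follow-up weight are included

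*Protocol article*

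**What the plan says.** The Data analysis section gives the methods for the two anthropometric primary outcomes: "Paired t-tests and repeated measures analysis will be used to examine the effect of the intervention on body weight and BMI of participants over time". The type of repeated measures analysis is not given. The same paragraph then sets the analysis populations: "The analysis will be conducted using intention-to-treat principles and for completers only". Completers are not defined.

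The Sample size section expects substantial loss: "an attrition rate of 30% was estimated between enrolment and follow up assessment, bringing the total sample size to 1303 participants".

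The Data collection section describes one group measured at baseline (T0), 12 weeks (T1), 6 months (T2) and 9 months (T3). There is no comparison arm and no randomisation. The article does not say how a participant without a follow-up weight enters the intention-to-treat analysis: it names no imputation, no carry-forward and no likelihood-based model.

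**The concern.** With a single group there is no allocated arm in which to keep people, so intention-to-treat can only mean that all enrolled participants are included. A paired t-test works on within-person differences and therefore needs both weights. Run on observed data, it describes only those who came back to be weighed, whatever label it carries.

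At stake is the meaning of the headline weight change. The Discussion section treats engagement and participation as the route through which the programme is expected to work. If that is right, people who disengage would tend to do worse, and they are also the people more likely to lack a follow-up weight. There is no control arm in which a similar attrition bias could cancel. If the handling of missing weights is left open, it could also be chosen after the data are seen.

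**Working it through.** **Inputs from the article (Sample size section).** The base figure is 871 people, chosen to show a 1.9 kg fall in weight with 90% power. The other test settings are stated as "at α = 0.05 and effect size of 0.11". The allowance for sites is stated separately: "An additional sample of 15% was added to account for unpredictable effect on statistical power of clustering cases by site". Attrition is 30% and the total is 1303.

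**Step 1: reproduce the article's figures.**
- A paired t-test with standardised effect 0.11, two-sided α = 0.05 and 90% power needs n = 871 (noncentral t). The normal approximation gives 868.4, and a one-sided test would need 710. So 871 is the two-sided paired t-test figure, and the paired comparison is the one that was powered.
- Site allowance: 871 × 1.15 = 1001.65, rounded up to 1002.
- Attrition allowance: 1002 × 1.30 = 1302.6, rounded up to 1303.

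Both stated figures reproduce. Multiplying by 1.30 is not the same as dividing by 0.70, but that is a separate matter and does not affect this point.

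**Step 2: who enters a paired t-test at the stated attrition.**
- With a pair: 1303 × 0.70 = 912.1, about 912.
- Without a pair: 1303 × 0.30 = 390.9, about 391.

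**Step 3: what the missing 30% could do to the mean.** Let stayers lose 1.9 kg on average and leavers lose g kg. The 1.9 kg is the article's difference to be detected, used here as an assumed loss in stayers. The values of g are also assumptions, because the article gives none.

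All-enrolled mean loss = 0.70 × 1.9 + 0.30 × g

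| Leavers' mean loss g (assumed) | All-enrolled mean loss | Stayers' mean exceeds it by |
|---|---|---|
| 1.9 kg (same as stayers) | 1.33 + 0.57 = 1.90 kg | 0 |
| 0 kg | 1.33 + 0 = 1.33 kg | 0.57 kg (0.57/1.33 = 43%) |
| −1 kg (a gain) | 1.33 − 0.30 = 1.03 kg | 0.87 kg (0.87/1.03 = 84%) |

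The difference is 0.30 × (1.9 − g). It is zero only if leavers change as stayers do.

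**The case against.** A reader might infer that both promised analyses are completer analyses, so that the intention-to-treat result must equal the completer result. The documents do not support that, for three reasons.

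- **The repeated measures analysis has no stated type.** A repeated-measures ANOVA with listwise deletion would keep only people seen at every visit. A linear mixed model uses every observed visit, including those of people lost later. The article does not mention ANOVA, and SPSS, the named software, can fit either.
- **Completers are undefined.** The word may mean finishing the programme rather than having a follow-up weight. A T0–T1 or T0–T2 paired test would also include people lost before T3, whom a completer set would normally leave out.
- **A paired t-test can be run on everyone enrolled once missing weights are imputed.** An article may leave the imputation rule to a full protocol or analysis plan, which is not shown here.

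It is also fair to say that informative loss is an inference. The article does not say that people who do badly, or who find work, will miss follow-up. The leaver outcomes in the table are assumptions, and one of them gives no bias.

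These points rule out a claim that the two results are necessarily identical. They do not remove the mismatch. The article fixes a test that needs complete pairs, sizes the study for that test, adds participants to cover those expected to be lost, and promises intention-to-treat without naming anything that would bring those participants in.

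**Conclusion.** The point stands in a limited form. Applied to observed weights, the paired t-test named in the article does not deliver the intention-to-treat estimate that the article promises. At the stated attrition about 391 of 1303 enrolled would not contribute. Unless their weights are modelled or imputed, the paired intention-to-treat and completer results would largely coincide, though they need not be equal.

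The 30% is the article's own figure. The size of any bias rests on the assumed change in leavers: across the range shown, a 1.9 kg loss in stayers corresponds to an all-enrolled loss of between 1.9 and 1.03 kg. The documents do not establish that a bias will occur or in which direction. They show that the method as worded would not protect against one. It should be settled before analysis, because it bears on a primary outcome and is cheap to correct.

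**What to change.** In the Data analysis section:

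1. Specify the repeated measures analysis as a linear mixed model (SPSS MIXED) of all observed weights at T0–T3, for everyone enrolled who has a baseline weight. Include visit as a categorical factor, site, and a participant random effect. Make this the intention-to-treat analysis in place of the paired t-test, and treat BMI in the same way.
2. Add one sensitivity analysis in which missing follow-up weights are imputed around the participant's own baseline (return to baseline). It is needed because the mixed model assumes that weights are missing at random. For someone who leaves before any follow-up, the model has only the baseline weight to work with. In the table above, return to baseline corresponds to the row with no loss in leavers.
3. Keep the paired t-test as a supportive analysis labelled completers only, and define completers.

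The cost is revised wording and some analyst time, in software already named and with no new data or visits. The downside for the sponsor is that the headline weight loss may be smaller.

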## Discussion

This paper is the first to use a mixed-methods realist evaluation to investigate the effectiveness of a novel health-related model targeted at individuals who are unemployed or living with obesity or overweight. ASPIRE is an innovative multicentre health-related and skills training programme with the aim of developing a model to holistically improve wellbeing, self-efficacy, reduce overweight, obesity and increase employment. While a consistent link between overweight, obesity and unemployment has been well established, the majority of interventions are still tailored to address these as separate entities. The ASPIRE model will regard these challenges holistically and use common strategies including improving self-efficacy, health and wellbeing and skills training to reduce overweight, obesity and unemployment. Several studies have shown the beneficial impact of reemployment on health, wellbeing and obesity [49–51] as well as the reverse impact of reducing obesity on employment outcomes [52].

The evaluation will examine which aspects of the ASPIRE model are working, for whom and in what circumstances. Both quantitative and qualitative data from the evaluation will be used to elucidate the processes of engagement and participation, which are hypothesised to mediate the programme’s success. The different contexts which enhance or reduce the uptake of intervention activities will be examined to inform how to refine existing weight and employability policies and programmes to improve their effectiveness, and how to adapt them to new contexts. Furthermore, the use of the realist approach will help to identify and test the hypothesised causal mechanisms, evaluate the extent to which ASPIRE activated them, use this analysis to refine the programme theory and identify areas of strength and potential future improvement in the programme design. The finalised theory would provide a better understanding of how mechanisms and contexts combine to generate the required outcomes in ASPIRE.

Strengths of this protocol include the use of a multidisciplinary and mixed-method realist evaluation approach to provide a better understanding of the complexity of interventions to reduce overweight, obesity and unemployment. Because of the complex and multifactorial causal factors underlying obesity and unemployment, interventions seeking to address these are equally complicated and require a comprehensive understanding of intervention context, implementation, mechanisms and outcomes which can be achieved using a realist evaluation approach. The pre-post evaluation method chosen will also minimise the effect of interindividual variation on outcomes.

In conclusion, the novel findings from this evaluation will contribute to international, European, national and regional strategies and policies to address the current challenges of obesity, overweight and unemployment. Additionally, experiences from the implementation of ASPIRE will be embedded in existing services to enhance the quality and effectiveness of interventions that individuals who are overweight, obese or unemployed can receive. Furthermore, participants and their families will benefit immensely through the maintenance of a healthy lifestyle and the model can be adapted by any community looking to make healthy lifestyle changes.

## Data Availability

Data sharing is not applicable to this article as no datasets were generated or analysed during the current study.

## Abbreviations

BMI: Body mass index
CMO: Context-mechanism-outcome
CBPR: Community-based participatory research
FCE: France Chanel England
FFQ: Food frequency questionnaire
GSE: General self-efficacy
PA: Physical activity
RE: Realist evaluation
WHO: World Health Organisation
